### Analysis

We will perform unadjusted bivariate comparisons of outcomes and predictors across intervention groups using t tests for continuous variables and chi-square tests for categorical variables. We will also conduct analysis adjusting for patient demographic characteristics, patient clinical characteristics, and the time period when the patient began follow-up. We will use logistic regression to model the Aim 1 primary outcome of whether or not a cost conversation occurred. In Aim 2, we will use linear regression to analyze outcomes with multi-level scales (e.g., decision regret scale [30]) and logistic regression to analyze binary outcome measures (e.g., collaboRATE [41]). To account for clustering of patient participants by urologic surgeon, we will estimate hierarchical models with urologic surgeon random effects. Let *Y*_*ijt*_ denote an outcome measured on the *i*th patient of the *j*th surgeon at time *t* and *OG*_*jt*_ indicate whether surgeon *j* has transitioned from usual care to the Option Grid (OG) by time period *t*. To lessen the reliance on the random assignment of surgeons to step times to balance any changes across time between the intervention groups, we adjust for the time period when the patient began follow-up, patient demographic and patient clinical characteristics. Adjustment for time period will be enabled by including indicator variables for time periods 2 through 5 (making time period 1 the excluded category) with effects denoted by {*λ*_*t*_}=_*t* = 2 : 5_ while all other patient-level variables will be included in a vector of covariates, denoted *X*_*ijt*_. Therefore, the model for the Aim 1 analysis and those outcomes modeled as binary random variables in Aim 2 has the form
1$$ logit\left(\Pr \left({Y}_{ijt}=1\left|{\theta}_j\right.\right)\right)={\beta}_0+{\beta}_1{OG}_{jt}+{\beta}_2{X}_{ijt}+{\lambda}_t+{\theta}_j $$

while the model for those outcomes modeled as continuous variables in Aim 2 has the form
2$$ {Y}_{ijt}={\beta}_0+{\beta}_1{OG}_{jt}+{\beta}_2{X}_{ijt}+{\lambda}_t+{\theta}_j+{\varepsilon}_{ijt} $$

where for both models *θ*_*j*_ is a random effect specific to surgeon *j* and for the linear regression model ∈_*ijt*_ is an idiosyncratic error term. The surgeon random effects and the error terms are assumed to be independent normally distributed random variables with unknown variance. Because 5 surgeons is a small number of units in which to estimate a random effect, as a sensitivity analysis we will estimate the generalized estimating equation alternative to these mixed effect models. We will favor the approach that yields the more conservative results.

We will check for outliers and missing data. If there is extensive missing data, we will use one of the following remedies: (1) inverse-probability weighting if there is a single form of missing data (e.g., only the outcome is missing) or (2) multiple imputation if missingness occurs sporadically across the outcomes and predictors. Analyses will follow the intention to treat principle. Where required to make the skewed distribution of a variable more symmetric, we will employ variable transformation.

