### Practical issues in performing the study

COVID-19 has impacted clinical research worldwide, with many non-urgent healthcare visits canceled, postponed, or moved to a telehealth format in early-mid 2020. These changes allowed for a lower risk of viral spread within healthcare facilities while directing healthcare resources to COVID-19 treatment. As COVID-19 infection counts stabilize, eligible patient volumes are beginning to return to pre-pandemic levels at the participating study setting. However, a second wave of the virus during the study period could limit our ability to recruit patient participants and meet accrual targets according to our planned timeline. Our inclusion of telehealth visits in this study has the potential to mitigate a slowdown of in-person patient recruitment; however, it can complicate the previously planned in-person procedures. We will document the number of patients seen via telehealth and in-person, and we will explore the potential impact of telehealth on outcomes.

The 2-year study timeline could limit our ability to assess outcomes at long term follow-up. As most active surveillance costs do not accrue immediately, financial toxicity data reported by patients on active surveillance at 3-month follow-up may not be comprehensive; we have therefore included financial toxicity as an exploratory outcome in this study.

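### Supporting t and chi-square tests of outcomes across arms are not labelled descriptive, and in this stepped wedge they confound the intervention with calendar time and ignore surgeon

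*Protocol article*

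**What the plan says.** The Analysis section of the protocol article begins: "We will perform unadjusted bivariate comparisons of outcomes and predictors across intervention groups using t tests", with chi-square tests where a variable is categorical. Two features matter. The comparisons cover outcomes, not only patient characteristics, and nothing says that they are descriptive.

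The next sentence adds: "We will also conduct analysis adjusting for patient demographic characteristics, patient clinical characteristics, and the time period when the patient began follow-up". The section then sets out the regression analyses:

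- Primary outcome of Aim 1: "We will use logistic regression to model the Aim 1 primary outcome of whether or not a cost conversation occurred". Aim 2 outcomes go to linear or logistic regression according to scale.
- Clustering: "To account for clustering of patient participants by urologic surgeon, we will estimate hierarchical models with urologic surgeon random effects".
- Calendar time: "Adjustment for time period will be enabled by including indicator variables for time periods 2 through 5".
- Sensitivity analysis: "as a sensitivity analysis we will estimate the generalized estimating equation alternative to these mixed effect models", with the more conservative of the two approaches to be favoured.

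Model equations (1) and (2) both contain the intervention indicator, patient covariates, period effects and a surgeon effect. No model is written down that keeps period and surgeon but leaves out the patient covariates. The only unadjusted effect in the plan is therefore the one from the plain tests.

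**The concern.** In a stepped wedge, arm and calendar time are tied together by construction: the first period has only control patients and the last only intervention patients. Randomizing surgeons to steps does not balance time between arms. The article gives as its reason for adjusting for period that this reduces reliance on that randomization. That presents a necessary term as a refinement and makes an unadjusted comparison look like a legitimate companion result.

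A pooled t or chi-square test attributes any change over time to the intervention. It also treats patients of the same surgeon as independent, although the sample size section assumes an ICC of 0.05. Change over time is plausible here. The section on practical issues says that visits were "moved to a telehealth format in early-mid 2020", that volumes were recovering, and that a second wave might come during the study. The early-mid 2020 change falls largely before or at the start of recruitment (24 June 2020), so the recovery and the possible second wave are the better grounds for expecting drift.

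At stake is a published unadjusted p-value that could be significant with no intervention effect, or could be pulled the other way by an opposite drift.

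**Working it through.** **Inputs from the article.** Four sequences, five 3-month periods, and the fifth surgeon placed in sequence 2 (Design). ICC 0.05, 200 patients, 33.3% versus 66.7%, power 0.804 two-sided (Sample size).

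**Assumptions.** One sequence crosses over at the start of each of periods 2 to 5, because Fig. 1 is not visible; the article does say that all surgeons begin in usual care. Accrual is even, 200/25 = 8 patients per surgeon-period. Alpha is 0.05. The drift sizes are also assumed.

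**1. Which analysis does the stated power belong to?** The standard stepped-wedge variance (Hussey and Hughes), with period effects and a surgeon random effect, is

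Var = Iσ²(σ² + Tτ²) / [(IU − W)σ² + (U² + ITU − TW − IV)τ²].

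Here I = T = 5, U = 13, W = 0 + 1 + 9 + 16 + 25 = 51 and V = 16 + 9 + 9 + 4 + 1 = 39. With total variance 0.25, τ² = 0.0125 and σ² = 0.2375/8 = 0.0297.

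Var = 5 × 0.0297 × 0.0922 / (14 × 0.0297 + 44 × 0.0125) = 0.01417, so the SE is 0.119. Power = Φ(0.3333/0.119 − 1.96) = 0.800, against 0.804 stated. The stated power agrees with a model that contains period and surgeon.

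**2. How far apart are the arms in time?**

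| Sequence | Surgeons | Intervention periods | Cells | Sum of period numbers |
|---|---|---|---|---|
| 1 | 1 | 2–5 | 4 | 14 |
| 2 | 2 | 3–5 | 6 | 24 |
| 3 | 1 | 4–5 | 2 | 9 |
| 4 | 1 | 5 | 1 | 5 |
| Total | 5 | | 13 | 52 |

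The intervention mean period is 52/13 = 4.00. All 25 cells sum to 5 × 15 = 75, so control is (75 − 52)/12 = 23/12 = 1.92. The gap is 2.08 periods, or 2.08 × 3 = 6.2 months. The intervention share by period is 0, 20, 60, 80 and 100%. A linear drift enters the raw difference at 2.08 times its per-period size: 5 points per period gives about 10 points.

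**3. Clustering alone, no drift.** Each surgeon's share of the intervention patients minus that surgeon's share of the control patients is 0.224, 0.064, 0.064, −0.096 and −0.256; the squares sum to 0.1335. The binomial factor is 1/104 + 1/96 = 0.02003. With the ICC on the proportion scale, the variance inflation is (0.95 × 0.02003 + 0.05 × 0.1335)/0.02003 = 1.283. The true rejection rate is then 2Φ(−1.96/√1.283) = 8.4%. With the ICC on the logit scale, the surgeon variance is (π²/3) × 0.05/0.95 = 0.173. At a rate of 1/3 this is a proportion-scale ICC of 0.222 × 0.173 = 0.0385, giving inflation 1.218 and a rejection rate of 7.6%.

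**4. Null simulation.** 40,000 trials per row, baseline 33.3%, logit-scale ICC 0.05, no intervention effect. The comparison analysis is a linear fit to surgeon-period proportions with surgeon and period effects, on a t reference with 15 degrees of freedom. It is a simple stand-in for models (1) and (2), not those models themselves.

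| Drift per period | Mean raw difference | Plain chi-square rejects | Period and surgeon in the fit |
|---|---|---|---|
| 0 | 0 | 7.5% | 5.2% |
| 2 points | 4 points | 12% | 5.0% |
| 5 points | 10 points | 32% | 4.9% |
| 8 points | 16 points | 62% | 5.4% |

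With ICC 0 and no drift the plain test rejects at 5.0%, so the excess comes from clustering and drift and not from the test itself.

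**The case against.** A reader might infer that plain tests decide this trial's outcomes, or that no main analysis is identified. The article does not support that. The Methods part of the Abstract names hierarchical regression with a surgeon random effect for patient-level outcomes and does not mention t or chi-square tests. The Analysis section ties the Aim 1 analysis to model (1) and the Aim 2 outcomes to (1) or (2). GEE is the sensitivity analysis to those models, and the rule on the more conservative result chooses between mixed model and GEE only; the plain tests have no part in it. The stated power fits a model with period and surgeon effects. All of this stands, and it makes the issue minor for the main inference.

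Two further objections stand in part. The rejection rates with drift rest on trend sizes that the article does not give; clustering alone gives only about 7.5% to 8.4%. And a condensed article may leave labelling to a fuller plan. But this is not only something left out: the article states a test of outcomes that is unsuitable for its own design, without qualification.

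**Conclusion.** The point holds as a modest one about supporting analyses. The main inference, from models (1) and (2) with GEE as sensitivity analysis, already handles both time and clustering and is not affected. What remains is that t and chi-square tests of outcomes are planned without being called descriptive, and their p-values are not valid here.

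The time gap of 2.08 periods follows from the design, given the usual one-step-per-period layout and even accrual. The false-positive rate of about 7.5% with no trend rests on the article's ICC, read on the logit scale. The figure of about 30% holds only under an assumed drift of 5 points per period and shows scale; it is not a forecast.

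**What to change.** In the Analysis section:

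1. Limit t and chi-square tests to describing patient characteristics.
2. Show outcomes by arm and by period, without p-values.
3. Define the unadjusted effect as model (1) or (2) with intervention, period indicators and surgeon effect, but no patient covariates.
4. State outright that models (1) and (2) are the primary analysis.

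The cost is a few sentences. No new data or larger sample is needed, and the unadjusted model is the planned one with the covariate vector left out.

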## Methods

### Design

This study uses a stepped-wedge cluster-randomized trial design (see Fig. 1) [19]. There are four sequences, with at least one cluster (urologic surgeon) randomized to each sequence. The fifth urologic surgeon will be assigned to the second sequence in order to balance patient accrual to the intervention and control arms. There are five periods, each lasting 3 months, for a total study duration of approximately 15 months. Independent eligible patients will be enrolled at each period within a cluster (urologic surgeon).

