### Sample size

We assume given the study timeline and projected patient volumes that it is feasible to recruit up to 50 patients from each of the five participating urologic surgeons, to target a total of 200 patient participants. Due to the novelty of our shared decision-making intervention intended to promote cost conversations in cancer care, limited data were available to inform the assumed ICC [14]. Based on the unmeasured clinician-level variability observed in other studies using similar interventions to study different outcomes, we conservatively assumed a relatively large ICC value of 0.05. Under these assumptions, and assuming an intraclass correlation coefficient of 0.05 for our primary outcome, the design effect of the stepped-wedge design equals 3.12, making the effective sample 32 per intervention group; this is the equivalent sample-size under a design in which there is no clustering of patients within surgeons [40].

In relation to Aim 1 and our primary research questions, prior research demonstrates that surgeons who used an encounter decision aid about early-stage breast cancer surgery with comparative cost information were far more likely to engage in cost conversations compared to those using a decision aid without cost information or those in usual care (66.7% versus 33.3%) [14]. Surgeons in the cost information decision aid group were also more likely to initiate these conversations compared to those in the non-cost information decision aid group (86.4% versus 34.1%) [14]. We estimated power directly for a stepped-wedge design. A requirement for performing this calculation is supplying the between-cluster variance. We estimated this quantity by solving for its value given the specified ICC of 0.05 and the within-cluster variance of a Bernoulli (binary-valued) random variable, whose mean equals the average value of the assumed probabilities of the outcomes for the two comparison groups (0.5, the most conservative value we could assume). The resulting power for a two-sided test was estimated to be 0.804. A projected sample size of 200 is therefore sufficient to answer our primary research questions.

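### The plan's remedy for having only five surgeons (a GEE alternative, then favouring the more conservative result) does not restore the nominal error rate and lets the results choose the estimator; the excess is modest

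*Protocol article*

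**What the plan says.** The Analysis section gives model (1) for the binary outcomes: a logistic model with an Option Grid indicator, period indicators, patient covariates and a normal random effect for surgeon. It then acknowledges the difficulty: "Because 5 surgeons is a small number of units in which to estimate a random effect". Its response is to fit a GEE version, labelled a sensitivity analysis, and to add: "We will favor the approach that yields the more conservative results". The section names no test statistic, reference distribution, variance estimator or significance level, and it does not define conservative.

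The layout is in the Design section: "There are four sequences, with at least one cluster (urologic surgeon) randomized to each sequence". With five surgeons for four sequences, one sequence holds two of them, and the section places the extra surgeon in sequence 2. On timing it says: "There are five periods, each lasting 3 months". The Sample size section supplies the planning values: "to target a total of 200 patient participants", "assuming an intraclass correlation coefficient of 0.05 for our primary outcome", rates of 66.7% and 33.3%, and a stated power of 0.804 for a two-sided test.

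**The concern.** The section sees the small-cluster problem but answers it with a method that usually tolerates few clusters less well. The usual GEE sandwich variance is estimated from the spread between clusters, and here there are five.

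The choice rule then raises two questions.

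- **Error rate.** If both candidates rely on large-sample inference, does taking the more cautious one bring the test back to its nominal level?
- **Definition.** More conservative could mean the larger p-value, the wider interval or the estimate nearer the null, and these can disagree. The logistic mixed model estimates an odds ratio conditional on surgeon, and GEE estimates a marginal one. The reported quantity therefore depends on the results, and it could differ from one primary outcome to the next. An analysis that can replace the main one is also no longer a sensitivity analysis.

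At stake are the stated certainty of the primary result and the prespecification of the analysis that produces it.

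**Working it through.** **Inputs from the article.** Five surgeons; five periods; surgeons cross over at periods 2, 3, 3, 4, 5; 200 patients, so 200/25 = 8 per surgeon-period if equal; ICC 0.05; rates 66.7% and 33.3%; mean rate 0.5, so Bernoulli variance 0.25. **Assumed:** two-sided 5%, z reference, no small-sample correction, and conservative meaning the larger p-value.

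**Step 1: the stated power.** The Hussey–Hughes variance is

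Var = I·s(s + Tτ²) / [(I·U − W)s + (U² + I·T·U − T·W − I·V)τ²]

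with I = T = 5, U = 13 (treated cells), W = 0 + 1 + 9 + 16 + 25 = 51, V = 16 + 9 + 9 + 4 + 1 = 39.

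- Total variance 0.25: τ² = 0.0125 and s = 0.2375/8 = 0.02969. Var = 5 × 0.02969 × 0.09219 / (14 × 0.02969 + 44 × 0.0125) = 0.01417, so SE = 0.1190. With a difference of 0.334, z = 2.806 and power = Φ(2.806 − 1.960) = 0.801.
- Within-surgeon variance 0.25: τ² = 0.01316, SE = 0.1221, power 0.781.

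The stated 0.804 is thus approximately reproduced with a normal critical value. With t on 15 df (critical value 2.131), the same two calculations give 0.746 and 0.725.

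**Step 2: false-positive rate under no effect.** Each simulated trial was analysed with model (1) without patient covariates (quadrature, z test) and with an exchangeable GEE (uncorrected sandwich, z test). The rule rejects only if both do. The Monte Carlo SE near these rates is about 0.25 points with 10,000 runs and 0.45 with 3,000.

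| Scenario | Runs | Mixed model | GEE alone | Larger-p rule |
|---|---|---|---|---|
| ICC 0.05, rate 1/3 | 10,000 | 7.0% | 27.5% | 6.6% |
| ICC 0.05, rate 0.5 | 10,000 | 7.0% | 27.9% | 6.6% |
| ICC 0.05, unequal volumes | 10,000 | 7.2% | 29.7% | 6.7% |
| ICC 0.05, cluster autocorrelation 0.5 | 10,000 | 7.8% | 28.2% | 7.2% |
| ICC 0.05 plus surgeon-by-period SD 0.4 logits | 3,000 | 9.1% | 27% | 8.5% |
| ICC 0.10, autocorrelation 0.5, unequal volumes | 9,999 | 11.2% | 29.9% | 9.8% |
| ICC 0 | 10,000 | 4.7% | 30.8% | 4.5% |

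Repeats of the base case with 3,000 runs each gave 6.4–6.9% for the mixed model, 28–28.8% for GEE and 6.0–6.5% for the rule.

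**Step 3: what the rule does.** It selects GEE in only about 13–21% of trials, because the mixed model usually has the larger p-value already. It therefore removes only 0.2 to 1.4 points across the 10,000-run scenarios. In one 3,000-run set, GEE was selected in 15% of null trials. Its SE there was a median 1.03 times the mixed-model SE, and its 95% interval missed the truth in 1.7% of those trials. With rates 1/3 and 2/3, the selected GEE intervals missed in 8.4% (median SE ratio 1.07).

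**Step 4: alternatives.** Residual df: 25 cells − 5 (intercept and periods) − 4 (surgeons) − 1 (treatment) = 15. Allocations: 5!/2! = 60 if all five surgeons are randomized, 4! = 24 if the fifth is not.

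| Test | Size at ICC 0.05 | Size with SD 0.4 effect | Power |
|---|---|---|---|
| Mixed model, z | 6.4–7.0% | 9.1% | about 0.79 |
| Mixed model, t on 15 df | 4.2–5.6% | 6.4–7.0% | 0.73–0.745 |
| Mixed model, t on 3 df | 0.3% | not run | 0.32 |
| Permutation, 60 allocations | 4.9–5.5% | 4.6% | 0.69–0.70 |
| GEE, Mancl–DeRouen SE, z | 8–10% | not run | not run |

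The size ranges for t on 15 df, t on 3 df, permutation and Mancl–DeRouen include scenarios with cluster autocorrelation below 1.

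**The case against.** Three stronger readings are tempting, and the documents do not support them.

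- **That the trial runs a 28% false-positive rate, or that a reported GEE interval would be far too narrow.** The plan favours GEE only when it is the more conservative result. In those trials its SE is about equal to or slightly above the mixed model's. The 28% belongs to GEE used alone, which the plan never does.
- **That choosing after seeing both results inflates the error.** Requiring both tests to reject can only lower the rate. The excess comes from the assumed z reference. Deleting the sentence and changing nothing else would raise the rate slightly.
- **That the article commits to an uncorrected Wald test or sandwich.** It says neither. A degrees-of-freedom method may stand in an analysis plan that is not shown, and its absence from a condensed article is not a fault.

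It can also be said that model (1) is written out and GEE is called a sensitivity analysis, so only a tie-break is loose. That is partly right, but the tie-break decides which estimate is reported. What stands is what the article itself fixes: GEE as the answer to having few clusters, and a results-dependent rule with an undefined criterion. A later plan could add a reference distribution, but it could not keep that rule and also have one prespecified estimator.

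The remedy has limits too. The df choice matters greatly (15 against 3), and t on 15 df does not fully repair the surgeon-by-period case.

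**Conclusion.** The point holds as a modest defect. At the protocol's own design and ICC, the favoured result would reject a true null in about 6.0–6.6% of trials instead of 5%, an excess of about 1 to 1.6 points. It would be about 8.5% with surgeon-by-period variation of SD 0.4 logits, which model (1) omits and for which the article gives no value. The reported odds ratio, conditional or marginal, would depend on the results.

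The figures rest on a two-sided 5% level, z inference without correction, conservative read as the larger p-value, no patient covariates, and an ICC above zero. The protocol assumes 0.05; at ICC 0 the mixed-model test holds its level.

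**What to change.** 1. Name model (1) as the single primary analysis, with a prespecified small-sample reference for the treatment coefficient, for example t on 15 df with the count shown. State the significance level.
2. Replace the sentence on favouring the more conservative approach with a statement that the primary analysis is reported whatever the sensitivity analyses show. Make this change together with item 1.
3. Keep GEE as a sensitivity analysis only, with both a small-sample variance correction and a t reference. Correcting the SE alone still left 8–10%.
4. Add a permutation test as a robustness check over the allocations that were actually possible. State whether the fifth surgeon's place in sequence 2 is randomized (60 arrangements, smallest p 1/60 = 0.017) or fixed (24 arrangements, smallest p 1/24 = 0.042). The Design section can be read either way.
5. Say that t on 15 df leaves about 6.4–7% if the surgeon-by-period effect of SD 0.4 is present. The permutation check held its level there (4.6%, with 60 allocations).

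The cost is a few sentences and minor programming. Power falls from about 0.79–0.80 to about 0.73–0.75 with t on 15 df, and to about 0.70 by permutation over 60 allocations. The stated 0.804, and the conclusion that 200 patients suffice, should be restated to match.

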**Other data**		
Treatment choice	Patient report	Immediately post-visit
Treatment received	Electronic health record	3 months post-visit
Health literacy (Single-Item Literacy Screener [35])	Patient report	Immediately post-visit
Patients’ other (comorbid) health conditions	Electronic health record	Immediately post-visit
Patients’ demographic characteristics	Patient report	Immediately post-visit

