### Outcomes

#### Primary outcomes

We will measure the frequency of cost conversations, initiator of cost conversations, and whether or not a referral is made to address costs. We will collect these primary outcomes by patient report from all participating patients in a questionnaire completed immediately post-visit (or shortly after a telehealth visit).

We will also use an existing observer checklist [14] to assess these outcomes for participating patients who consent to audio-recording their clinic visits. We will use Hunter et al.’s approach to defining a cost discussion: “any mention of the patient’s out-of-pocket expenses or insurance coverage for a past, present, or potential health care service” [26]. For example, any mention of costs or insurance coverage for primary surgery, radiation, imaging, as well as indirect costs of care such as time off work, transportation, recovery time, will be documented and included in our analyses. If direct or indirect costs are mentioned per Hunter’s definition [26], we will indicate that costs were discussed during the consultation. If there are two mentions of cost in one transcript, with a different topic in between, the mentions will be coded as two cost discussions. If costs are discussed at all, the subsequent items (length of time of the cost conversation, number of times cost was discussed, who initiated the cost discussion, content of cost discussions, whether a referral is made to address costs) will then be evaluated. We will document references to the Option Grid to examine whether the Option Grid directly prompted the cost conversation. Because we do not expect surgeons to know specific details about treatment costs, the checklist also includes an item to measure whether a referral is made to address more detail about costs. We will document to whom a referral is made (navigator, social worker, outside resource).

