#### Data collection

##### Observational data

For participating patients who agree during the study consent process to audio-recording of their in-person clinic visits, the study coordinator will start a digital recorder when the patient enters the exam room and return to collect the recorder at the end of the clinic visit. Where participating patients agree to audio-recording of their virtual visits, audio-recordings will be captured by the urologic surgeon through Zoom or other HIPAA-compliant telemedicine software and subsequently transferred securely to the study coordinator.

Audio-recordings will be transcribed verbatim for analysis. Two members of the study team will independently review each transcript and apply the observer checklist [14, 26] to identify frequency and initiator of cost conversations and frequency of referrals to address costs.

At the time of patient enrollment, study staff will review the electronic health record to determine whether or not the participant has been diagnosed with each of the 20 most common and costly health conditions, as described in the Medical Panel Expenditure Survey [37–39], and record those comorbidities in the study’s Research Electronic Data Capture database (REDCap). At 3-month follow-up, study staff will collect the patient’s received treatment (if any) from the electronic health record and record that information in REDCap.

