##### Patient-reported data

We will administer post-visit patient questionnaires at two timepoints: immediately after the clinic visit and 3 months after the clinic visit. At both timepoints, study staff will collect patient-reported data by emailed link to an online survey form hosted in REDCap or by standardized telephone interview, depending on participant preference. All questionnaire data will be stored in REDCap and response modality will be recorded. Study staff will make up to five attempts to contact patient participants for response to each survey.

After completion of the first post-visit questionnaire, study staff will mail patient participants a $15 gift card. After completion of the second questionnaire at 3-month follow-up, study staff will mail patient participants a $5 gift card.

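### For the post-visit outcomes, demographics and health literacy come only from the questionnaire that carries the patient-reported outcomes, so a wholly missing questionnaire leaves weighting or imputation without them

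*Protocol article*

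**What the plan says.** **Source of the covariates.** Under Other data, Table 2 of the protocol article reads "Patients’ demographic characteristics Patient report Immediately post-visit" and "Health literacy (Single-Item Literacy Screener [35]) Patient report Immediately post-visit". No other source or time is listed for either. The Outcomes section says that Table 2 summarizes all study measurement, planned covariates included.

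**Source of the primary outcomes.** "We will collect these primary outcomes by patient report from all participating patients in a questionnaire completed immediately post-visit". A second, observer-coded version exists for patients who consent to audio-recording.

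**Follow-up of non-responders.** "Study staff will make up to five attempts to contact patient participants for response to each survey".

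**Use of the covariates.** In the Analysis section, "we adjust for the time period when the patient began follow-up, patient demographic and patient clinical characteristics".

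**Missing data.** If missingness is extensive, the Analysis section names two remedies. One is "inverse-probability weighting if there is a single form of missing data (e.g., only the outcome is missing". The other is multiple imputation when values are missing sporadically over outcomes and predictors.

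**What is already collected earlier.** "At the time of patient enrollment, study staff will review the electronic health record", in order to record comorbid conditions.

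**The concern.** Weighting for non-response needs variables that are known for responders and non-responders alike. Here the demographics, which the adjusted models call for, arrive with the outcome or not at all. Whole-questionnaire non-response is therefore a block of missing outcome and missing predictors. It is not a case in which only the outcome is missing, and it is not obviously sporadic.

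Three things are at stake:

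- Weights or imputation for these patients cannot draw on their demographics or literacy, although willingness to answer a survey about costs could plausibly vary with such characteristics.
- A non-responder whose visit was recorded has an observed primary outcome but no demographics for the adjusted model.
- Responders cannot be compared with non-responders on demographics by arm. Patients see whether they receive the Option Grid, so response could differ between arms.

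The adjustment has a real job in this trial. Five surgeons are allocated by simple randomization, and the Analysis section says it adjusts so as to depend less on that allocation for balance over time.

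**Working it through.** **Plan's own figures.** None is in dispute, and the point changes none. For completeness, the effective sample is 200 / 3.12 / 2 = 32.05, matching the stated 32 per group. The stated power of 0.804 is reproduced closely by the Hussey-Hughes variance:

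- Inputs: I = 5 surgeons, starting in sequences 1, 2, 2, 3 and 4; T = 5 periods; 8 patients per cell; ICC 0.05 of a total variance of 0.25, so τ² = 0.0125 and σ² = 0.2375/8 = 0.0297; difference 0.334; two-sided alpha 0.05 (assumed, not stated).
- Design sums: U = 13, W = 51, V = 39.
- Variance = Iσ²(σ² + Tτ²) / [(IU − W)σ² + (U² + ITU − TW − IV)τ²] = 0.01368 / 0.9656 = 0.01417.
- Power = Φ(0.334/0.1190 − 1.96) = 0.801.

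**What each kind of patient has, reading Table 2 against the Data collection section:**

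| Patient | Patient-reported post-visit outcome | Demographics, literacy | Chart data, surgeon, period, arm | Observer-coded outcome |
|---|---|---|---|---|
| Answers first survey | yes | yes | yes | if recorded |
| Answers first, misses 3-month survey | yes (3-month outcome missing) | yes | yes | if recorded |
| Never answers first survey, not recorded | no | no | yes | no |
| Never answers first survey, recorded | no | no | yes | yes |

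Row 2 is the situation the weighting example describes: only the 3-month outcome is missing and every covariate is in hand. Rows 3 and 4 are the gap. In row 3 outcome and demographics go together. In row 4 the observed outcome is present and the predictors are missing.

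**What remains for rows 3 and 4.** Comorbidities from the chart; Gleason score, PSA or surgeon referral, from the eligibility check; visit mode, which the Discussion says will be documented; treatment received, from the chart at 3 months; surgeon, period and arm. Row 4 adds the recording.

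**Counts.** The article gives no response rate. Assuming 10% to 25% never answer, 200 × 0.10 = 20 and 200 × 0.25 = 50 patients fall in rows 3 and 4. How many fall in row 4 depends on recording uptake, also not given, so it lies anywhere from 0 to that total.

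**Illustration of why the missing variable can matter (all inputs invented).** Let 30% have a demographic trait D and 40% a chart condition C, independently. Set Pr(outcome) = 0.4 + 0.2D + 0.1C and Pr(response) = 0.9 − 0.3D − 0.1C.

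- True mean: 0.4 + 0.06 + 0.04 = 0.500. Response: 0.9 − 0.09 − 0.04 = 0.77.
- Responders only: covariance −0.06 × 0.21 − 0.01 × 0.24 = −0.015, so 0.500 − 0.015/0.77 = 0.481 (simulated 0.482).
- Weighted on C alone: 0.500 − 0.0126 × (0.6/0.81 + 0.4/0.71) = 0.484 (simulated 0.485).
- Weighted on C and D: 0.500 (simulated 0.502, against a simulated truth of 0.501).

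Weights on chart data alone recover little of the shift when response depends on D. The example concerns an overall mean and has no arms. It says nothing about bias in the intervention effect.

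**The case against.** The plan does not rest on weighting alone. That remedy is conditional on extensive missingness, the outcome-only case is given as an example, and multiple imputation is planned for gaps that span outcomes and predictors. Whether a whole missing questionnaire counts as sporadic is a detail that an analysis plan not shown here could settle. This stands, but it does not supply the values: imputation cannot condition on demographics that were never recorded for those patients.

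The stronger objection concerns bias. The demographics are in the outcome model. If response depends only on modelled covariates, arm, surgeon and period, complete-case regression still estimates the adjusted intervention effect consistently, and the loss is one of precision. If response depends on the outcome itself given those covariates, earlier capture of demographics would not by itself cure it. This also stands. What is left is unadjusted comparisons, variables outside the model, and the recorded non-responders.

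Further points are fair. Five contact attempts, a choice of online or telephone completion, and a $15 gift card should keep non-response down. Table 2 does not itemize the demographics. The role of literacy as an adjuster is inferred, since the Analysis section names only demographic and clinical characteristics. Staff already have access to the health record, so the gap may be recoverable later.

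**Conclusion.** The point holds for the post-visit outcomes, as a modest weakness in data capture and not as a contradiction in the plan. By Table 2, whole-questionnaire non-response removes the patient-reported primary outcomes together with demographics and literacy. Response weights or imputation for those patients can then rest only on the chart, visit-mode and design data and any recording.

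A reader might infer more, and the article does not support it:

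- *That the weighting fails for every outcome.* It works as written for the 3-month outcomes of patients who answered the first survey.
- *That all adjustment covariates are lost.* The clinical ones come from the chart.
- *That recorded outcomes are lost outright.* They drop out only under complete-case analysis; otherwise the demographics must be imputed.
- *That the adjusted effect must be biased.* It need not be, for the reason given in the objection.

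The size is unknown. The figure of 20 to 50 patients rests wholly on an assumed 10% to 25% non-response among 200, and the number of recorded non-responders cannot be stated without the recording uptake.

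**What to change.** Extract the core demographics that the health record holds during the chart review already done at enrolment for comorbidities. Keep the self-reported value where the questionnaire is returned. Where it is missing, use the chart value for adjustment and for response weights or imputation. State that whole-questionnaire non-response will be handled in this way, and compare responders with non-responders by arm on the chart variables. Asking the single literacy item at consent is optional.

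The cost is a few more fields in a review already planned, with no new visit. The drawback is that race as recorded in the chart may be less accurate than self-report, which is why self-report should take precedence when available.
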